#### Total cost of the treatment

We will calculate the total cost of the participants’ treatment at week 48.

### Safety evaluation

We will monitor blood regular test, urine regular test, liver function test (AST, ALT, alkaline phosphatase/ALP, gamma-glutamyl transpeptidase/γ-GT, total bilirubin/TBIL), renal function test (creatinine/Cr, urea), and electrocardiogram (ECG) to certify whether Mingjing granule could be safe. Patients will be asked to report to the researchers any abnormal reactions occurring in the trial. All details of related and unexpected adverse events, such as time of occurrence, degree and duration, suspected causes, and the effective measures and outcomes will be recorded on CRF. Any ocular or systemic adverse events will be treated suitably and recorded accurately and completely as well.

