#### Statistical methods

All the efficacy and safety analyses will be conducted within the full analysis set (FAS) according to the intention-to-treat principle, with all randomly assigned participants included. Last-observation-carried-forward method will be applied in the missing values. We will conduct the per-protocol set (PPS) analysis to compare the results from FAS and PPS, and safety set (SS) will be used for the safety evaluation. Data from the six centers will be combined for statistical analysis of the primary and secondary outcomes as well as adverse events. Demographic, eye examination, and laboratory characteristics will be calculated at baseline, intervention, and follow-up period. The mean ± standard deviation will be chosen for continuous variables and the comparison between the two groups will be analyzed by *t* tests with normal distribution. Non-parametric Mann-Whitney-Wilcoxon test will be used for the comparison of data with non-normal distribution. Categorical variables will be compared using *χ*^2^ statistics, while the Fisher exact test will be used when the theoretical frequency is less than 5 in more than 25% of the cells. In order to control the center and baseline effects, covariance analysis will be applied for the intergroup comparison with continuous variables and Cochran-Mantel-Haenszel test for categorical variables. All statistical tests are unilateral tests; *P* < 0.05 means statistically significant. All statistical analyses will be performed by using SPSS V.19.0.

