In summary, this protocol describes a randomized controlled trial conducted in 6 centers to evaluate the efficacy and safety of Mingjing granule in the treatment of AMD. If results of this trial demonstrates that Mingjing granule combined with ranibizumab has better efficacy, less injection times, and lower cost and good safety, it will provide useful clinically information for AMD and offer patients and ophthalmologists a new treatment option.

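### The only inference stated for safety is one-sided difference tests with no direction given, which at 90 per group cannot establish the safety that the protocol promises

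*Protocol article*

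**What the plan says.** Safety is half of the trial's stated aim (Protocol article, Abstract and Background). Four places bear on how it will be judged.

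- **Safety evaluation:** blood, urine, liver and renal tests and ECG are monitored "to certify whether Mingjing granule could be safe". Adverse events are recorded with timing, degree, suspected cause, measures taken and outcome.
- **Discussion, closing paragraph:** the results the trial might demonstrate are that the combination "has better efficacy, less injection times, and lower cost and good safety".
- **Statistical methods:** adverse events go to formal analysis: "Data from the six centers will be combined for statistical analysis of the primary and secondary outcomes as well as adverse events". Continuous variables get t or Mann-Whitney tests. Categorical variables get chi-square, and "the Fisher exact test will be used when the theoretical frequency is less than 5 in more than 25% of the cells". Then, for everything: "All statistical tests are unilateral tests; *P* < 0.05 means statistically significant". No direction is stated.
- **Sample size:** the calculation rests on best-corrected visual acuity alone.

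Statistical methods first places all efficacy and safety analyses in the full analysis set, then says "safety set (SS) will be used for the safety evaluation".

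**The concern.** The verb in the safety section promises a verdict, and the Discussion repeats it as a possible result. The tools supplied answer a different question. A difference test that rejects shows a difference. One that does not reject leaves open every excess inside the confidence interval, and in a trial sized for a visual acuity mean that interval is wide for event counts.

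The one-sided rule makes this worse. It covers all tests and has no stated direction. If the direction is that of the superiority hypothesis (granule better), then for adverse events the rejection region lies entirely on the side of fewer events on the granule. An excess of harm of any size would return a non-significant P value.

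At stake is the safety half of the conclusion. A moderate real excess of, say, liver enzyme abnormalities would often be non-significant, and nothing in the article stops that result from being reported as support for safety.

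**Working it through.** **1. The plan's own figure.** Sample size inputs: difference 10.1 − 8.2 = 1.9 letters, SD 4, Z values 1.96 and 0.84.

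n = 2 × 4² × (1.96 + 0.84)² / 1.9² = 69.5, so 70 per group. The t-based version gives 70.5, so 71, which matches the article. With 20% dropout, 71 / 0.8 = 88.75, so 89; 90 per group are planned. The figure reproduces, and no safety quantity enters it.

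**2. Chance of missing a true excess of events.** Inputs from the document: 90 per group; chi-square, or Fisher when expected counts fall below 5; P < 0.05. Assumed inputs: the event rates (placebo v granule), because the article gives none, and a one-sided test pointing toward harm, because no direction is given.

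Method: list all pairs of counts (x on granule, y on placebo), weight each by Bin(x; 90, p_T) × Bin(y; 90, p_C), apply the test, and add up the weight where P is not below 0.05. Fisher is used when (x + y)/2 is below 5, otherwise the pooled z test (the chi-square test in its one-sided form). The second figure is the two-sided 0.05 miss rate, which is in effect also the rate for a one-sided test at the α = 0.025 used in the sample size section.

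- 1% v 5%: missed 73% (84%)
- 0% v 5%: missed 53% (71%)
- 2% v 8%: missed 51% (64%)
- 5% v 10%: missed 65% (77%)
- 10% v 20%: missed 39% (53%)
- 5% v 15%: missed 25.5% (37%)
- 5% v 20%: missed 6% (11%)

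Excesses of 4 to 6 points are missed about half to three-quarters of the time under the stated one-sided threshold. Excesses of 10 to 15 points are mostly detected.

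**3. The same test in the superiority direction.** It rejects only when the granule has fewer events than placebo. Any result with more events on the granule gives a one-sided P above 0.5, so the chance that an observed excess is declared significant is zero, whatever its size.

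**4. What a non-significant result leaves open.** Suppose 4/90 on granule and 0/90 on placebo. One-sided Fisher P = C(90,4)/C(180,4) = 0.060; two-sided 0.12. Neither is below 0.05. The observed excess is 4.4 points, and its Newcombe 95% interval runs from −0.5 to +10.9 points.

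**5. What estimation would support instead.** With zero events in 90, the one-sided 95% upper bound is 1 − 0.05^(1/90) = 3.3%. With equal observed rates p in both groups, the upper limit of the two-sided 95% interval for the excess is about 1.96 × √(2p(1 − p)/90): 4.1 points at 2%, 6.4 at 5%, 8.8 at 10%.

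**The case against.** The strongest reply is that the article nowhere sets the rule being criticised. A reader might infer that safety will be certified by P > 0.05, but the safety section mentions no test, the Discussion sentence is conditional, and the statistical section lists general-purpose tests. Adverse events are also recorded in detail, which allows case-by-case judgement. This stands: the text does not support the claim that the investigators will read non-significance as safety. What remains is that the article states a conclusion and a set of tests, and nothing in it turns those tests, or the recorded case details, into that conclusion.

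A second reply is that a harm margin, a safety sample size, confidence intervals and counts of abnormal values are commonly left to the full protocol or analysis plan. This also stands, and their absence is not the point here. The point is what the article does fix: one-sided tests for everything, and wording stronger than such tests can carry.

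A third reply is that the miss rates depend on chosen event rates. That is correct. It would be tempting to say that a clinically important excess would usually be missed, or that the safety conclusion would hardly depend on whether the granule is harmful. Neither holds in general: 5% v 15% and 5% v 20% would mostly be detected by a test toward harm. Nor should the figure of 71 per group be used for safety, since it is the evaluable number for visual acuity, not a safety set.

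Finally, laboratory means are not the weak spot. A shift of 0.5 SD would be missed only 4.5% of the time with 90 per group, one-sided toward harm. The limitation concerns event and abnormality counts.

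**Conclusion.** The point holds as a mismatch between a stated purpose and a stated method. One-sided difference tests at P < 0.05 with 90 per group cannot certify safety. Under assumed rates and a test toward harm, excesses of about 4 to 6 points are missed roughly 51% to 73% of the time, while excesses of 10 to 15 points are missed roughly 6% to 39% of the time. If the unstated direction is that of superiority, no excess can ever be significant; the article does not say which direction applies, so this is a possibility and not an established fact.

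The sizes rest on assumed event rates, on all 90 per group being in the safety analysis, and on the article's rule for choosing chi-square or Fisher. That a difference test cannot establish safety does not depend on any of these. The matter should be corrected before analysis; it does not threaten the primary efficacy comparison.

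**What to change.** In **Statistical methods**:
- Exempt safety from the rule that "All statistical tests are unilateral tests".
- Report adverse events, serious adverse events and laboratory or ECG abnormalities as counts by group, with the risk difference and a two-sided 95% confidence interval.
- State that a non-significant difference is not evidence of safety.
- Name the safety set as the population for these tables and remove the sentence's conflicting assignment of safety to the full analysis set.

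In **Safety evaluation**, replace the certifying aim with describing the safety profile and estimating differences in event rates.

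In the **Discussion**, limit any statement of good safety to what the upper confidence limits exclude. For example, zero events of a given type among 90 excludes only rates above about 3.3% (one-sided 95%).

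The cost is wording and a few extra table columns, with no new data and no additional patients. The price is a more modest safety statement.

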### Ethics and dissemination

#### Patient consent and dissemination policy

This trial will be complied with the Declaration of Helsinki and Ethical Guidelines for Clinical Research. We will rigorously follow the latest Consolidated Standards of Reporting Trials (CONSORT 2017). The protocol has been permitted by the Research Ethical Committee of Eye Hospital, China Academy of Chinese Medical Sciences, Foshan Hospital of Traditional Chinese Medicine, Shenzhen Traditional Chinese Medicine Hospital, Henan Province Hospital of Traditional Chinese Medicine/The Second Affiliated Hospital of Henan University of Chinese Medicine, The Second Affiliated Hospital of Liaoning University of Traditional Chinese Medicine, The Affiliated Hospital of Shandong University of Traditional Chinese Medicine/Shandong Province Hospital of Traditional Chinese Medicine, and The First Teaching Hospital of Tianjin University of Traditional Chinese Medicine. The results of this study will be disseminated to the public through academic conferences and peer-reviewed journals.

#### Access to data and confidentiality

Privacy of participants will be highly respected in the conduct of the study. The personal information about the potential and enrolled participants will be collected to be used only in this trial. All data will be kept strictly confidential at the study site. Only research team members will have access to the research data. All local databases will be secured with password-protected access systems. Any data required to support the protocol can be supplied on request. Forms, lists, appointment books, and any other listings that link participant ID numbers to other identifying information will be stored securely with limited access. The information of participants will not be released and shared without the written permission of the participant.

#### Sample size

We design a superiority trial with a ratio of 1:1. The primary outcome is the mean change of BCVA at week 48 as compared to the baseline. After reviewing some literature, the mean change of BCVA in the test group is expected to increase by 10.1 letters measured by ETDRS chart, which in the control group is expected to increase by 8.2 letters [39, 40]. *n*_*c*_ is the participants’ number in each group. σ (standard deviation of the two groups) = 4. *Z*_1−*α*_ = 1.96, when *α* = 0.025; *Z*_1−β_ = 0.84, when *β* = 0.2. Δ = 0, *K* = 1, μ_T_ = 10.1, μ_C_ = 8.2. We calculate it by the PASS software; there are 71 cases in each group. Considering a 20% drop-out rate, there are 89 cases in each group and a total of 178 cases in both groups. Thus, we plan to recruit 180 participants in total (30 cases in every center, 15 cases in each group). The sample size calculation formula is as follows [41]:
$$ {n}_c=\frac{{\left({Z}_{1-\upalpha}+{Z}_{1-\upbeta}\right)}^2{\sigma}^2\left(1+1/K\right)}{{\left({\mu}_T-{\mu}_C-\Delta \right)}^2} $$

#### Statistical methods

All the efficacy and safety analyses will be conducted within the full analysis set (FAS) according to the intention-to-treat principle, with all randomly assigned participants included. Last-observation-carried-forward method will be applied in the missing values. We will conduct the per-protocol set (PPS) analysis to compare the results from FAS and PPS, and safety set (SS) will be used for the safety evaluation. Data from the six centers will be combined for statistical analysis of the primary and secondary outcomes as well as adverse events. Demographic, eye examination, and laboratory characteristics will be calculated at baseline, intervention, and follow-up period. The mean ± standard deviation will be chosen for continuous variables and the comparison between the two groups will be analyzed by *t* tests with normal distribution. Non-parametric Mann-Whitney-Wilcoxon test will be used for the comparison of data with non-normal distribution. Categorical variables will be compared using *χ*^2^ statistics, while the Fisher exact test will be used when the theoretical frequency is less than 5 in more than 25% of the cells. In order to control the center and baseline effects, covariance analysis will be applied for the intergroup comparison with continuous variables and Cochran-Mantel-Haenszel test for categorical variables. All statistical tests are unilateral tests; *P* < 0.05 means statistically significant. All statistical analyses will be performed by using SPSS V.19.0.

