**Methods/design:**

This is a double-blind, placebo-controlled, randomized trial of Mingjing granule as an add-on to intravitreous ranibizumab for nAMD. One hundred eighty nAMD patients from six hospitals in China will be enrolled according to the inclusion and exclusion criteria and randomly allocated into two groups, 90 in each. All participants will receive a 24-week treatment and then be followed up for another 24 weeks. The primary outcome is the mean change of best-corrected visual acuity at week 24 and 48 as compared to the baseline. The secondary outcomes include mean change in central retinal thickness, area of retinal hemorrhage and exudation, and TCM syndrome score, mean number of intravitreal ranibizumab injection, and total cost of the treatment. Indexes of safety include blood regular test, urine regular test, liver function test, renal function test, and electrocardiogram from baseline to weeks 24 and 48. Qualitative control and some standard operating processes will be formed throughout the trial. Any ocular or systemic adverse events will be treated suitably, and related data will be recorded accurately and completely in the case report form.

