## Methods

### Trial design

This is a randomized, double-blind, placebo-controlled trial. Participants will be randomly allocated into two groups, the test group and the control group. Patients in the test group will receive Mingjing granule plus ranibizumab, while those in the control group will receive placebo with ranibizumab. All of them will be followed up every 4 weeks. Mingjing granule and placebo will be dispatched every 4 weeks until week 24; ranibizumab will be administered as needed after three consecutive monthly injections until week 48 (Figs. 1 and 2). The protocol is designed following the guidelines of the Consolidated Standards of Reporting Trials and Standard Protocol Items: Recommendations for Interventional Trials (SPIRIT) (see Additional file 1 SPIRIT 2013 checklist). The trial has been registered with the Chinese Clinical Trial Registry (ChiCTR2000035990, registered on 21 August 2020).

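### The Statistical methods section assigns safety to two different populations and, as worded, extends LOCF and one-sided tests of unstated direction to safety data

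*Protocol article*

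**What the plan says.** The relevant rules stand together in one paragraph of the protocol article, under Statistical methods.

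- **Population, first statement:** "All the efficacy and safety analyses will be conducted within the full analysis set (FAS) according to the intention-to-treat principle". The sentence goes on to include every randomised participant.
- **Population, second statement:** the "safety set (SS) will be used for the safety evaluation".
- **Missing data:** "Last-observation-carried-forward method will be applied in the missing values". Nothing restricts this to efficacy variables.
- **Tests:** "All statistical tests are unilateral tests; *P* < 0.05 means statistically significant". Nothing exempts safety, and no direction is given.

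On timing, the abstract lists the laboratory indexes, ending with "renal function test, and electrocardiogram from baseline to weeks 24 and 48". The Safety evaluation section gives no laboratory times. The Trial design section says "All of them will be followed up every 4 weeks" and has the granule or placebo dispensed until week 24. Adverse events are captured separately: "Any ocular or systemic adverse events will be treated suitably and recorded accurately and completely as well".

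**The concern.** Three separate defects sit in the same paragraph.

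1. **Population.** A full analysis set of all randomised participants and a safety set can differ in denominator (participants who never took a dose) and possibly in grouping (as randomised or as treated). Because the first sentence covers all safety analyses, the second cannot be read as a supplement to it. Left unresolved, the denominator could be chosen after the results are known.
2. **LOCF.** Carrying values forward reports a laboratory or ECG result at a time when it was not measured. If week 24 is the only scheduled on-treatment sample, the value carried to week 24 for an earlier leaver may predate treatment.
3. **Sidedness.** A one-sided test needs a direction. The trial is framed as a superiority trial, and nothing says whether that direction also applies to adverse events and laboratory comparisons.

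Safety is a declared aim. The Safety evaluation section says the tests are meant to establish whether the granule is safe, and the closing summary makes good safety part of the result that would support its use.

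**Working it through.** The plan gives no safety rate to reproduce. Its only related figure is the drop-out allowance in the Sample size section, which does reproduce: 71 / (1 − 0.20) = 88.75, rounded up to 89 per group; 2 × 89 = 178, recruited as 180, or 90 per group.

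**Step 1: the two population sentences.** One places all safety analyses in the set of all randomised participants. The other places the safety evaluation in the safety set. The two agree only if everyone randomised is treated, and treated as allocated, which a plan cannot presume. The numerical effect is probably small. Assuming 2 of 90 never take a dose and 6 have an abnormality, 6/88 = 6.8% becomes 6/90 = 6.7%.

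**Step 2: does LOCF reach safety data?** The LOCF sentence directly follows the one naming efficacy and safety analyses, and it has no restriction. The same paragraph goes on to summarise laboratory characteristics. Read literally, it applies.

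**Step 3: what LOCF could do.** Inputs from the article: 90 per group and 20% drop-out, so 0.20 × 90 = 18 per group might lack a later laboratory value. This is an upper figure for week 24, since the allowance covers the whole trial. Assumptions: laboratory tests only at baseline, week 24 and week 48; baseline values not classed as abnormal; and a share *s* of those who become abnormal leave before week 24 with no further sample. The displayed rate is then (number abnormal) × (1 − *s*) / 90.

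| Abnormal of 90 (assumed) | True rate | *s* = 0 | *s* = 0.5 | *s* = 1 |
|---|---|---|---|---|
| 3 | 3.3% | 3.3% | 1.7% | 0% |
| 6 | 6.7% | 6.7% | 3.3% | 0% |
| 9 | 10.0% | 10.0% | 5.0% | 0% |

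The understatement runs from nothing to complete, depending wholly on *s*, which the document does not fix.

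**Step 4: sidedness.** Take an assumed 6 versus 0 of 90 and Fisher's exact test. Toward harm, the one-sided P is C(90,6) / C(180,6) = 0.014. The two-sided P, with equal groups, is twice that, 0.029. In the opposite direction, the one-sided P is 1.0. The same data are therefore significant or wholly unremarkable depending on a direction that the plan does not state.

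**The case against.** A reader might infer more than this: that patients who withdraw with toxicity will be displayed with normal values, that toxicity is erased, and that the tests cannot detect harm. The document does not support those statements.

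- **Sampling times are not established.** The schedule figure is not available here, visits are every 4 weeks, and the Withdrawal criteria link withdrawal for complications to a need for safety evaluation. A sample at or before withdrawal is not ruled out.
- **A measured signal would be carried forward.** Someone who leaves because of a raised liver enzyme has had it measured, and nothing limits LOCF to scheduled values. That abnormal result would be the last observation. Only changes that were never sampled can be hidden.
- **Baseline need not be normal.** The Exclusion criteria remove only liver enzymes and creatinine at twice the upper limit of normal or above.
- **Adverse events are recorded independently.** Time, degree, duration, suspected cause and outcome go on the case report form, and adverse events are included in the pooled analysis.
- **No direction is stated.** A one-sided test aimed at harm is more sensitive than a two-sided one (0.014 against 0.029 in the example).
- **The causes are separate.** Any masking comes from LOCF combined with sparse sampling. The population conflict and the sidedness rule do not produce it.

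All of this stands, and it narrows the point. It does not remove the contradiction between the two population sentences, nor does it make LOCF or an undirected one-sided rule suitable for safety data. The membership of the safety set and the detailed table layouts may properly be left to the full protocol or analysis plan, and their absence from the article is not counted here.

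**Conclusion.** The point holds as a wording defect with conditional consequences.

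- **Certain from the text:** safety is assigned to two populations, and neither LOCF nor one-sided testing is limited to efficacy. The effect of the population conflict on rates is likely to be trivial. The objection is to leaving the choice open.
- **Conditional on sampling only at baseline and weeks 24 and 48:** LOCF would understate abnormalities in the laboratory and ECG summaries for those who leave before week 24 without a further sample. In the assumed example, 6.7% would be shown as anything from 6.7% down to 0%. Adverse event reporting is not affected.
- **Conditional on the benefit direction carrying over:** a one-sided test could not flag excess harm. If it does not carry over, the direction is undefined. Both readings need correcting.

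This does not undermine the trial's conduct or its primary efficacy comparison. It should be corrected before unblinding, while the choice of safety denominator is still independent of the results.

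**What to change.** Amend the Statistical methods paragraph as follows.

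1. Delete the words *and safety* from the sentence on the full analysis set, so that safety is analysed in the safety set, meaning treated patients.
2. State that LOCF applies to efficacy variables at most.
3. Report laboratory and ECG data as observed, including any unscheduled or withdrawal values already collected, with tables of the worst post-baseline shift.
4. Exempt safety from the one-sided rule. Make its comparisons descriptive, or give differences with two-sided 95% confidence intervals.

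The cost is a change of wording and some minor extra tabulation. No additional visits, samples or participants are needed, because only values already collected are used.

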#### Withdrawal criteria

In cases of worsening disease or concomitant complications with a necessity of safety evaluation and curative treatment.With the forbidden therapy and medication history during the trial, which will lead to bias for efficacy and safety evaluation.

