#### Concomitant medications

Participants in both groups will receive 3 consecutive monthly intravitreal injections of ranibizumab (allowed to be injected at a dose of 0.5 mg per time). If necessary, they will be reinjected another during the followed up period. Decision for the reinjection will be guided on the criteria formulated by prospective OCT imaging of patients with neovascular AMD treated with intraocular ranibizumab (PrONTO) [38]: (1) a loss of 5 letters or more, (2) an increase in central retinal thickness (CRT) at least 100 μm, (3) new retinal hemorrhage appears, (4) new typical CNV, (5) fluid still exists after injection last month, and (6) any qualitative increase in the amount of fluid.

Participants will be requested not to receive any other treatments for nAMD, such as complementary treatments (e.g., herbal medicine, and acupuncture) or other medications, throughout this study. Participants will be allowed to take western medicine to treat the systematic diseases, such as hypertension or heart disease. The use of all drugs, if any, will be documented in detail in the case report form (CRF).

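### Last observation carried forward is the only missing-data method while worsening disease is a ground for withdrawal, so the week 48 BCVA comparison may be biased, in either direction

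*Protocol article*

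**What the plan says.** All references are to the protocol article.

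- **Statistical methods.** Efficacy is analysed in the full analysis set "according to the intention-to-treat principle, with all randomly assigned participants included". For gaps, "Last-observation-carried-forward method will be applied in the missing values". The only other efficacy analysis set is per protocol, to be compared with the full analysis set.
- **Withdrawal criteria.** There are two grounds: "In cases of worsening disease or concomitant complications with a necessity of safety evaluation and curative treatment", and "With the forbidden therapy and medication history during the trial, which will lead to bias for efficacy and safety evaluation".
- **Sample size.** "The primary outcome is the mean change of BCVA at week 48 as compared to the baseline". Expected gains are 10.1 letters (test) and 8.2 letters (control), with SD 4. The number per group is then raised: "Considering a 20% drop-out rate".
- **Primary outcome.** BCVA is assessed at baseline and at weeks 24 and 48, with further examinations possible when needed.
- **Trial design.** "All of them will be followed up every 4 weeks".
- **Concomitant medications.** One ranibizumab reinjection criterion is "a loss of 5 letters or more".

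**The concern.** The first withdrawal ground is close to the primary outcome itself, and the second (turning to another therapy) may follow from a poor response. For a patient who leaves on either ground with no later BCVA recorded, the plan enters an earlier score (baseline, week 24 or a later interim visit) as the week 48 result. LOCF then assumes that vision would not have changed after that score. The article's own background describes AMD as progressive, and its Discussion says that relapse is common once anti-VEGF treatment stops, so this assumption is hard to defend for patients withdrawn because they were worsening.

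The planned difference is only 1.9 letters and up to one fifth of week 48 values may be filled in, so a modest difference between arms in who leaves, and why, could matter. Including every randomised patient does not cure this, because the analysis keeps the patient but not the patient's week 48 outcome. The per-protocol comparison does not test the assumption either, since withdrawn patients would probably be left out of that set.

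**Working it through.** **Inputs from the Sample size section.** Difference 10.1 − 8.2 = 1.9 letters; SD 4; alpha 0.025 one-sided; power 80%; drop-out 20%; 90 per arm recruited. The Statistical methods section instead tests one-sided at 0.05, so both levels are shown.

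**The plan's own figure.** n = (1.96 + 0.84)² × 4² × 2 / 1.9² = 250.88 / 3.61 = 69.5, so 70 per group. The t-test version gives 70.5, so 71 as stated. With drop-out, 71 / 0.8 = 88.75, so 89. The stated sample size reproduces; it serves here only to give scale.

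**Bias formula.** Let w be the share of an arm withdrawn with week 48 filled in, and g the carried score minus the true week 48 score.

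Bias in the difference (test minus control) = w_T × g_T − w_C × g_C.

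The article gives neither w nor g, so every value below is an assumption.

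- *Equal w and g in both arms:* the bias in the difference is 0, although each arm mean is still shifted by w × g. Over w = 5% to 20% and g = 5 to 15 letters, that shift runs from 0.05 × 5 = 0.25 to 0.20 × 15 = 3.0 letters.
- *5-point imbalance, g = 10:* 0.05 × 10 = 0.5 letter; 0.5 / 1.9 = 26%. With 90 per arm, 5 points is 4.5 patients.
- *10-point imbalance, g = 10:* 0.10 × 10 = 1.0 letter; 1.0 / 1.9 = 53%. This is 9 patients.
- *5-point imbalance, g = 5:* 0.05 × 5 = 0.25 letter; 0.25 / 1.9 = 13%.

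The sign follows the imbalance. If more control patients are withdrawn for worsening, LOCF shrinks the difference; if more test patients are, it enlarges it.

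**Effect on power when the difference shrinks.** Normal approximation, SE = 4 × √(2/90) = 0.596; power = Φ(difference / SE − z).

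| Apparent difference | Difference / SE | Power, one-sided 0.025 | Power, one-sided 0.05 |
|---|---|---|---|
| 1.9 (no bias) | 3.19 | 89% | 94% |
| 1.4 (bias −0.5) | 2.35 | 65% | 76% |
| 0.9 (bias −1.0) | 1.51 | 33% | 45% |

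**When g is negative.** A patient who leaves early and has baseline carried forward is given a change of 0. Had that patient gone on to the expected average gain, g would be 0 − 8.2 = −8.2 letters in the control arm or 0 − 10.1 = −10.1 in the test arm. LOCF then understates that arm. This is one more reason why the direction cannot be fixed in advance.

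**The case against.** The strongest reply is that the size rests entirely on assumed inputs. The article does not say how much of the 20% drop-out is due to worsening, nor how many letters are lost afterwards. With matching rates and gaps the bias cancels, and if the granule works, more control patients may worsen, so that LOCF shrinks the difference and is conservative for superiority. All of this stands; it limits the claim to a possible bias of unknown sign and size.

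Four stronger readings are tempting, and the document does not support them.

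- *The carried score is always vision before the worsening.* Visits are 4-weekly and a reinjection criterion needs letter scores, so the last score may come from the visit that detected the decline. The schedule figure is not available here. The bias is then smaller, though any later decline is still missed.
- *The false-positive rate is inflated.* If the granule affects neither vision nor withdrawal, randomisation and blinding make the carried scores comparable between arms and the test keeps its level. Inflation needs a granule that leaves vision unchanged yet shifts withdrawal, and nothing in the article indicates that.
- *Standard errors are too small.* The test uses the sample variance of the carried scores, which may be larger or smaller than that of true week 48 scores. The article does not settle which.
- *Worsening triggers both withdrawal and reinjection, so the two sections contradict each other.* The withdrawal wording is tied to a need for safety evaluation and curative treatment and may describe a different threshold. What can be said is that the article draws no line between the two.

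It can also be said that an article may leave follow-up after withdrawal to the full protocol. That is fair: its absence is not counted as an error here. The method that the article does state, LOCF alone, is the point.

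**Conclusion.** The point holds in limited form. LOCF is a weak sole method where withdrawal can depend on the outcome, and it may bias the week 48 comparison in either direction. Under the assumed 5 to 10 point imbalance and 10-letter gap, the shift is 0.5 to 1.0 letter, against a planned 1.9. Under equal withdrawal and equal gaps it is zero. These figures illustrate sensitivity and do not estimate the bias to expect. The change should be made because a better method is available at little cost, and because week 48 scores not collected at the time cannot be recovered later.

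**What to change.** 1. **Primary analysis.** Replace LOCF with a mixed model for repeated measures on all recorded post-baseline BCVA changes: weeks 24 and 48 at least, and the 4-weekly scores if they are recorded. Include treatment-by-visit, baseline-by-visit and centre, and read the treatment contrast at week 48. Multiple imputation is an acceptable alternative.
2. **Sensitivity.** Both methods assume that data are missing at random, so add a delta-adjusted or reference-based analysis for patients withdrawn for worsening. Keep LOCF as a supportive analysis only.
3. **Data collection.** State that BCVA is still measured to week 48 after treatment stops or a withdrawal criterion is met, unless consent is withdrawn.
4. **Consistency.** Reconcile the Withdrawal criteria (worsening disease) with the reinjection criteria under Concomitant medications (letter loss), so that centres apply them alike. Where the line falls is a clinical decision for the sponsor and investigators.

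The cost is wording in the protocol and analysis plan, modest programming (SPSS fits mixed models), and some extra visits for patients who would otherwise have left.
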